### Power, sample size, and retention

The primary outcome for this intervention is child eating habits and dietary intake. Both the expected clinical effect of the intervention and variability of the primary outcome measure are important considerations. Thus, sample size calculations were based on Australian data by Mathews et al. that provide relevant parameter estimates from three studies in the Barwon-South Western region of Victoria (*n *= 950) with children aged 2-4 years of age [60]. Vegetable consumption will require the largest sample size to demonstrate change over time, compared to other dietary outcomes, such as sweetened drinks, packaged snacks (e.g., chips, muesli bar), confectionary/chocolate, cake/sweet biscuits, and fruit, based on sample size analyses. As there are no quantitative dietary recommendations for children less than 4 years old in Australia, we adopted Campbell et al.'s suggestion of a 25% increase in vegetable consumption as a minimum target [61]. Based on Mathews et al.'s finding that 63% of pre-school children had ≤1 serve of vegetables per day [60], we assume that the intervention will have a 25% absolute effect, that is the proportion of children in the intervention group who only have ≤1 serve of vegetables per day will change from 63% to 43%. We calculated the sample size necessary to detect a clinically meaningful difference in vegetable consumption, significant at the 0.05 level, with a power of 0.8; this calculation resulted in a sample of 100 parents in each group. Making a prudent allowance for attrition of 20% (attrition in a large longitudinal study with multiple time points over a 3-year period by Clark et al. [62]) the adjusted number per treatment condition is 120. A total of 240 parents of 2-4 year old children will therefore be recruited at baseline to allow for a final sample of 200. The final sample size of 200 participants is also sufficient to detect medium effect sizes in the secondary measures with a power of 0.8 at α = 0.05 [63]. Every CI on this research team has had experience in retention of participants in longitudinal studies. To facilitate retention we will build rapport with the participants by a regular newsletter and advance notification of assessments. To increase retention rates the CIs have found two measures are very helpful: 1) Parents who remain in the study will be entered into prize draws for gift vouchers. The amount needs to include a large grand prize plus multiple minor prizes. Prizes will be drawn each year. 2) Birthday cards will be sent out to each child participant.

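### The 20% attrition allowance was added as 100 × 1.2 instead of 100 / 0.8, so 240 recruits leave 192 families, not the stated 200

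*Protocol article*

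**What the plan says.** All the figures are in one paragraph of the protocol article, under Power, sample size, and retention. The calculation concerns the proportion of children having at most one serve of vegetables a day, 63% falling to 43% with the intervention. The effect is to be "significant at the 0.05 level, with a power of 0.8", and "this calculation resulted in a sample of 100 parents in each group". A 20% attrition allowance follows, taken from a longitudinal study with several time points over three years, after which "the adjusted number per treatment condition is 120". The paragraph then concludes: "A total of 240 parents of 2-4 year old children will therefore be recruited at baseline to allow for a final sample of 200". The next sentence uses that final 200 to claim power of 0.8 for medium effects on the secondary measures.

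**The concern.** An attrition rate is a fraction of those enrolled, so the recruitment target is the number needed at the end divided by one minus the rate. The plan instead adds 20% of the final number. The three stated figures (20% attrition, 240 recruited, 200 remaining) therefore cannot all be true.

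At stake is the number of completers behind the primary power calculation, which the secondary-outcome power statement also cites. It is the benchmark against which retention and achieved power will later be judged. A trial that lost exactly the planned 20% would appear to have missed its own target by 8 families. The Analyses section runs the primary analyses once on observed data, so the number remaining is what that analysis would have to work with.

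**Working it through.** **Inputs, all from Power, sample size, and retention:** p1 = 0.63, p2 = 0.43, α = 0.05, power 0.80, 100 per arm before attrition, attrition d = 0.20, 120 per arm after it, 240 recruited, 200 final. The section does not state the sidedness or name the test. I take a two-sided comparison of two proportions with pooled variance under the null. The attrition arithmetic does not depend on these choices.

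**Step 1. Reproduce the base sample size.** With mean proportion p̄ = (0.63 + 0.43)/2 = 0.53,

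n = [1.960 × √(2 × 0.53 × 0.47) + 0.842 × √(0.63 × 0.37 + 0.43 × 0.57)]² / 0.20²
= [1.960 × 0.7058 + 0.842 × 0.6915]² / 0.04 = 96.6, so 97 per arm.

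The unpooled formula gives 94, the arcsine formula 97 and the continuity-corrected formula 107. The stated 100 is consistent with 97 rounded up.

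**Step 2. Reproduce the attrition adjustment.**

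| Method | Per arm | Total |
|---|---|---|
| n × (1 + d) = 100 × 1.20 | 120 | 240 |
| n / (1 − d) = 100 / 0.80 | 125 | 250 |

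The plan's 120 is obtained exactly by the first line, not by the second.

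**Step 3. What 240 recruits deliver.**

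- Remaining after 20% attrition: 240 × 0.80 = 192, or 120 × 0.80 = 96 per arm.
- Shortfall against the stated final sample: 200 − 192 = 8 families, 4 per arm.
- Attrition that 240 can absorb while leaving 200: 1 − 200/240 = 16.7%.

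**Step 4. Effect on primary power.** Power = Φ{[0.20 × √n − 1.960 × 0.7058] / 0.6915}.

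| n per arm | Power |
|---|---|
| 100 | 81.4% |
| 97 | 80.2% |
| 96 | 79.8% |

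The slip costs 81.4 − 79.8 = 1.6 percentage points.

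**Step 5. Effect on the secondary-outcome statement.** Reading a medium effect as a standardised difference of 0.5 (my assumption), a two-sided t-test has 94.0% power at 100 per arm and 93.1% at 96.

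**Step 6. Room to absorb the loss.** The Procedure section delivers the intervention in groups of 6 to 10 dyads, and the sample-size paragraph mentions no allowance for clustering. Assume groups of 8, an intraclass correlation of 0.05 and clustering in the intervention arm only. The design effect there is 1 + 7 × 0.05 = 1.35, and 96 per arm then gives about 71–74% power, depending on the approximation. With an intraclass correlation of 0.01 or 0.02 the figures are 78.4% and 77.0%. Neither the correlation nor the group size of 8 is in the sample-size text, and nearly all of this fall is due to clustering, not to the attrition slip.

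**The case against.** The case on the other side accepts the arithmetic and disputes its importance.

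- **The loss of power is trivial and depends on the formula.** With an unpooled test, 96 per arm gives 80.9%, still above target, because the requirement is then 94. Rounding 97 up to 100 absorbs almost all of the shortfall. This stands, and it limits the size of the point.
- **The secondary-outcome claim is unaffected.** This also stands. Power of 0.8 for a standardised difference of 0.5 needs only 64 per arm. The stated basis of 200 is wrong, but the conclusion drawn from it is not.
- **The clustering figure belongs elsewhere.** Largely accepted. It shows that the plan has little slack; it does not measure this error.
- **The 20% may be cautious.** It comes from a three-year study, whereas this trial follows families for 10 weeks plus 12 months, and the Procedure section reports low attrition in pilot work. Attrition of 16.7% or less is plausible. That is a reason to state a lower rate, but it does not make 20%, 240 and 200 agree.
- **Multiple imputation and covariate adjustment are planned.** Imputation keeps every participant in the analysis but does not in itself restore the information lost with missing outcomes. Covariates may add precision, but the sample-size paragraph takes no credit for them.

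**Conclusion.** The concern holds. Under the plan's own 20% attrition, 240 recruits leave 192 families (96 per arm), and nothing elsewhere in the article reconciles this with the stated 200. That part is plain arithmetic and needs no assumption.

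The effect on power is modest: 79.8% instead of 81.4% for 63% versus 43%, assuming a two-sided pooled test and no clustering. That is just under the stated target of 0.8. The secondary-outcome statement survives. The figure should be corrected because it is stated wrongly and later retention will be measured against it; the trial is not materially underpowered by this slip alone.

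Two other discrepancies nearby are separate points and lend no weight to this one: the effect is described as 25% absolute although 63% to 43% is 20 points, and the Participants section allocates 200 parents where this paragraph recruits 240.

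**What to change.** Keep recruitment at 240 and restate the outcome: with 20% attrition, 192 families (96 per arm) are expected to remain, giving 79.8% power for 63% versus 43% before any allowance for clustering. Use the same 192 in the sentence on secondary measures.

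An acceptable alternative is to keep the final 200 and say that 240 recruits allow for attrition of 16.7%, with a reason for expecting that rate. If 200 completers after 20% attrition are a firm requirement, the recruitment figure is 250 (125 per arm).

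Either of the first two options costs one reworded figure that reads slightly less favourably, with no change to design or analysis. The third costs 10 more families.

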
### Analyses

We will adhere to 'intention-to-treat' principles following CONSORT Statement guidelines to prevent introduction of systematic bias [34]. As such, baseline data will be secured prior to treatment allocation, missing values will be scrutinized to check for non-random distribution and primary analyses will be executed twice: once using observed data, and once using multiple imputation under multivariate normal assumptions using methods given by Schafer [64], so that all participants will be analysed in their allocated condition. Analyses of covariance (with "other relevant variables" from above as covariates) will test the between group differences in the primary and secondary outcomes at each assessment time point and across time points for the parents and children. Finally, the interview transcripts will be analysed using elements of phenomenology and thematic content analysis [65], as demonstrated by Clark et al. and Powell et al. [66,67].

## Discussion

Obesity has reached epidemic proportions in Australia and calls have been made for strategies to reverse this unhealthy trend [68,69]. Early prevention of obesity, that is, developing effective prevention and intervention programs for the formative preschool years, is seen as one essential step in combating the obesity epidemic across the lifespan [70]. The preschool years have been identified as a critical period in childhood for the development of childhood obesity [71] because the eating and physical activity habits that contribute to later obesity become established during these formative years [72,73]. Targeting preschool aged children is central to preventing obesity, because development at this life stage is more malleable than it is in later childhood and adolescence [47], and risk factors of overweight can be more easily modified [74]. Despite these findings, there is a paucity of strategies aimed directly at preschool children [70,75]. This study aims to address this urgent need to develop and test the effectiveness of prevention programs for children at the preschool age. Such prevention programs need to be family-based [76], because the primary social force that influences young children's health behaviour and development is the parent [17,37]. Our intervention will provide information to parents and support them to establish and/or maintain healthy behaviours and attitudes around diet and physical activity for themselves and their preschool child(ren). If effective, this program could protect children from the development of obesity and its associated psychological, social and economic costs. Furthermore, this study has the potential to strengthen our knowledge base of health-promoting strategies that can be aimed at parents, which will hopefully lead to future national and international policy changes in relation to obesity prevention as well as the promotion of change at a global level.
